### Qualitative analysis

Qualitative interview data will be handled using the NVivo 12 software package and analysed using a framework approach informed by the literature about the challenges of clinical trial methodlogy.^59–63^ Initial thematic tables are likely to include elements such as randomisation and outcome measures. Table summaries will be used to generate recommendations about the nature and form of the subsequent trial; specific detail will also be used to inform recruitment strategies, data collection regimes and participant information resources.

### Data management and monitoring

Electronic data records will be stored in a SQL Server database, stored on a restricted access, secure server maintained by the University of Leicester, with access permission allocated by the Leicester Clinical Trials Unit (LCTU) IT team. Data monitoring for quality and completeness, including source data verification on a sample of documents, will be conducted by LCTU staff. The study documents shall be archived at secure archive facilities subcontracted to NUH. Data will be stored for 5 years.

Given this is a feasibility trial, the Data Monitoring Committee is included as part of the majority independent Trial Steering Committee (TSC), comprising two clinical experts and a statistician. The TSC will review trial progress, addressing study-related problems, assessing the safety of participants and ensuring timely publication of the study findings.

### Harms

All AEs will be reviewed by the chief investigator (CI) and recorded as part of the study outcome measures with an assessment of severity, relation and expectation. All deaths occurring up to the final study visit and serious AEs, other than expected surgical complications, will be recorded on the Sponsor SAE Form and faxed/emailed to the Sponsor and LCTU within 3 days of a researcher becoming aware of the event. Those related to the study and unexpected will be reported to the REC within 15 days. Events will be followed up until resolved or a final outcome has been reached.

The intervention in this trial is not testing a new surgical treatment. Therefore, serious expected sacroplasty surgical complications including wound infection, cement leakage causing nerve root damage and rarely pulmonary embolus will be captured in the Case Report Form (CRF), but do not require expedited reporting.

## Ethics and dissemination

### Patient and public involvement

Two members of the Royal Osteoporosis Society’s Nottingham support group represent the Patient and Public Involvement (PPI) for this study. Two focus groups have been held to inform the research, design and specific study outcomes. The PPI representatives have provided input into the grant application, study design and reviewing all participant facing documents. They will continue to provide input into trial conduct, as members of the Trial Management Group. They will assist with dissemination of study findings through their Royal Osteoporosis Society local communications as well as national contacts and support writing of the definitive future trial research grant application.

### Dissemination policy

Dissemination will include publication of the protocol methodology, with results being submitted for presentation at scientific meetings and conferences aimed at clinicians working with older people, trauma and spinal surgery (as well as being available on the NIHR RfPB website). Relevant patient groups and policy makers will be informed of the results, supported by our PPI engagement strategies.

If the findings indicate that a full-scale definitive trial is feasible, the data will be used to prepare an application for funding a large-scale definitive clinical and cost effectiveness randomised controlled trial, with the aim to change standard practise for the benefit of patient outcomes.

### Study registration and approvals

All study material has received approval from the Research Ethics Committee (REC—North East; Newcastle & North Tyneside 2, reference number 18/NE/0212), Health Research Authority (HRA) and the Nottingham Queens Medical Centre Research & Innovation department. Nottingham University Hospitals NHS Trust will act as sponsor to this study. The study has been registered on a clinical trials database (https://www.isrctn.com, reference number ISRCTN16719542, pre-results).

## Discussion

The growing older person population confers a large group of potential patients with complex medical and social needs, both in terms of medical comorbidities, susceptibility to hospital acquired complications and dependency. With the numbers of PFFs set to exponentially increase in the coming years, the potential healthcare resource burden within this group of patients is alarming. A recent systematic review concluded that randomised controlled trials were required to develop evidence-based protocols to reduce morbidity and mortality in older people with PFF.^22 33 64^ Given that keyhole spinal sacral fixation is already an established treatment option with a sound safety record, we propose that surgical management should be considered earlier in the treatment of PFF in older people admitted to hospital. This is to maximise early pain management with the aim of preventing pain-related immobilisation and its short and long-term consequences.

In order to ensure that the outcome of a clinical trial in this area has a high level of validity, it must be delivered within the constraints of the existing healthcare service, where the burden of patient care falls. This feasibility trial, delivered within this existing healthcare service, will analyse the outcomes posed by some of these constraints, to ensure that a future definitive trial is able to answer the clinical question efficiently. The inclusion of an economic evaluation will also demonstrate whether surgical fixation offers value for money as well as clinical effectiveness, an important consideration for existing services.

Potential limitations of delivering a clinical trial of this kind within an active healthcare service include identification of the sacral fractures themselves. Any patient presenting with an anterior pelvic ring fracture would need to be referred for further imaging in order to identify sacral fractures and thus be considered within the eligibility criteria for this trial. However, as standard care for patients presenting with PFF is currently conservative care, clinicians may feel that further imaging would not change a patient’s treatment course and thus be an unnecessary expense. As an identified sacral fracture is a key requirement for the eligibility criteria, this clinician assessment may significantly affect recruitment.

The target cohort in question may also provide further recruitment barrier. Cognitive impairment is common (up to 67%) in older patients presenting to hospital with PFF.^5 17 25^ As these patients confer such a large proportion of the real world PFF cohort, it would severely affect the validity of the trial to exclude them. Therefore, we have included a consent process for those patients that lack capacity. Identification is by AMT as a surrogate marker of capacity, which is completed as part of the clinical assessment of all admitted patients and therefore does not add any unnecessary burden prior to recruitment. Patients without capacity are reliant on the presence of relatives or carers to act as personal consultees, which may add a logistics barrier and reduce the recruitment of this subset of participants. Participants with cognitive impairment that are recruited may also be less likely to complete data collection due to difficulty with engagement, introduce detection bias due to issues with recall and may be more likely to be lost to follow-up.

Even once randomised, our participants remain under the existing healthcare service’s care for the entirety of the trial and are therefore at risk of protocol deviations due to the pragmatic setting of the study. The final decision to receive any intervention remains the responsibility of the patient’s clinical teams. For participants in the surgical intervention group, the decision to operate remains with the surgical team and may be susceptible to influence from factors such as surgeon experience and preference, belief in the clinical equipoise and theatre availability. Participants in the non-surgical (standard care) group may still be reviewed for surgical intervention based on clinical need identified by their clinical team, as determined by current practice. In order to assess the effect of this limitation, quantification and analysis of adherence to randomisation is an important outcome of this feasibility study.

An area of confounding not specifically assessed in this feasibility trial is the possibility of variation in the usual care received by all participants in both groups. This is not set by the protocol and while minimised by using a single site setting, where staff are working from the same local guidelines, resources and practices, variation is likely inevitable due to the non-regimented workings of a real-world healthcare service. The effect of these innate differences could be further minimised by using analysis of variation in outcome measures from this feasibility trial in order to power a future definitive trial appropriately.

This study is not powered to test the hypotheses, but the data collected will be able to provide a descriptive analysis on effectiveness of outcomes in order to inform analysis in a future definitive trial. The key outcomes address questions posed by the possible limitations of conducting such a trial within an existing public health service, specifically to recruitment and adherence to randomisation. The future aim is that the feasibility trial will advise a valid and fully powered randomised controlled trial to test the hypothesis that surgical intervention in PFF is of clinical benefit to patients as well as being cost effective and safe.

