**Trial registration number:**

ISRCTN16719542; Pre-results.

Strengths and limitations of this studyDescriptive analysis on effectiveness of outcomes will inform hypothesis testing in a future definitive trial, including levels of variability in order to power the trial appropriately.Nested semistructured interview study will provide valuable qualitative data to inform future definitive trial acceptability and processes.Determines the feasibility of economic measures including detailed resource use collection and quality of life data within the two arms, to aid the design of more comprehensive economic evaluation in a future definitive trial.The intervention is a proven safe surgical intervention, already used in existing healthcare practice, but further safety data in this cohort of patients will also be collected.A pragmatic trial set in an existing healthcare setting that may lead to a number of limitations on trial processes, including recruitment, adherence to randomisation and ease of data collection.

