### Objectives

The feasibility and final design of a definitive trial will be determined by fulfilment of the objectives outlined below. These are to:Determine the number of patients who meet the eligibility criteria in addition to recruitment (including willingness to be randomised) and retention rates of randomisedpatients.Explore the adherence of clinicians to the randomisation of patients within the trial.To collect outcome measure data for the assessment of mobility, pain and quality of life (face to face and self-reported measures), for potential use in a future definitive trial; estimate the mean and SD of these quantitative measures for hypotheses testing purposes.Evaluate ease of access and availability of information from current primary and secondary care databases, to determine the most efficient way of measuring associated patient level resource use.Use a qualitative nested interview study to assess participants’ and clinicians’ views on trial acceptability and processes to inform the design and conduct of a future definitive trial.Evaluate long-term safety of the intervention.

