### Study design

The primary study design is a parallel, two-arm randomised controlled feasibility trial with participants allocated to either surgical or non-surgical intervention on a 1:1 ratio. A preliminary economic evaluation and a qualitative nested interview study will also be embedded within the feasibility study.

Participants will be recruited from a single site, Queens Medical Centre (QMC), Nottingham University Hospitals NHS Trust (NUH), a university teaching hospital serving a population of 700 000 and offering a tertiary spinal surgical unit.

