### Data analysis

Data analysis will primarily be descriptive to address the aims of the feasibility study. A statistical analysis plan will be agreed prior to database lock and a CONSORT flow diagram produced. Data analysis overall will inform future trial feasibility and the hypothesis analysis plan for a definitive trial.

Characteristics of participants recruited will be summarised using appropriate descriptive statistics and compared with patients who were eligible but not randomised. Completeness of data collection will be reported by intervention group and overall.

Descriptive summaries of outcome data at each follow-up time point will be presented by intervention group and overall. Outcome distributions for suggested floor and ceiling effects will be checked. Confidence intervals will be presented for the proportion of patients consented, randomised and retained in the trial completing assessment at 12 weeks, both overall and by treatment group. Confidence intervals for the SD of the secondary outcomes will also be calculated where appropriate.

Exploratory analysis of continuous outcomes for the subsequent definitive trial will be performed to investigate potential treatment effects. Differences in mean values between baseline and 12 weeks will be presented, with 95% CI. This feasibility trial is not powered to perform hypotheses testing; however, descriptive statistics of the difference between randomised groups will inform the design of the main definitive trial. No subgroup analyses are planned, and no interim analyses will be performed aside from routine checks of safety data.

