### Health economic analysis

The within-trial economic evaluation will determine the cost-effectiveness of the surgical intervention compared with non-surgical (standard) treatment from an NHS and Personal Social Services perspective. The evaluation will follow the reference case guidance for technology appraisals as set out by NICE.^58^ Effectiveness will be captured using quality adjusted life years (QALYs) as assessed by the EQ-5D-3L.^48^ The primary outcome of the evaluation will be the incremental cost-effectiveness ratio (ICER) per additional QALY (ICER) gained from surgical fixation compared with standard care. Sensitivity analyses will be performed to control for uncertainty, which will include one-way and two-way sensitivity analyses on (but not exclusively) age, gender and baseline scores, with a probabilistic sensitivity analysis to control for all uncertainty. Results of the sensitivity analyses will be presented as tornado plots, 95% CI for the ICER and cost-effectiveness acceptability curves.

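### The protocol says the within-trial economic evaluation will determine cost-effectiveness, which conflicts with its own preliminary, unpowered status; about 43 completers are unlikely to support a firm conclusion

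*Protocol article*

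**What the plan says.** Two places in the protocol article give the economic component a conclusive purpose.

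- Health economic analysis: "The within-trial economic evaluation will determine the cost-effectiveness of the surgical intervention compared with non-surgical (standard) treatment". The same section continues: "The primary outcome of the evaluation will be the incremental cost-effectiveness ratio (ICER) per additional QALY (ICER) gained".
- Discussion: "The inclusion of an economic evaluation will also demonstrate whether surgical fixation offers value for money as well as clinical effectiveness".

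Other places give it a narrower one.

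- Study design: "A preliminary economic evaluation and a qualitative nested interview study will also be embedded within the feasibility study".
- Strengths and limitations box: the economic measures are there to have their feasibility checked, "to aid the design of more comprehensive economic evaluation in a future definitive trial".
- Objectives: the economic item is to evaluate data sources "to determine the most efficient way of measuring associated patient level resource use". Quality-of-life data are collected for possible later use. No objective is to establish cost-effectiveness.
- Data analysis: "This feasibility trial is not powered to perform hypotheses testing". Discussion: "This study is not powered to test the hypotheses". The Discussion then assigns the question of clinical benefit, cost-effectiveness and safety to a future, fully powered trial.

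**The concern.** A reader of the Health economic analysis section alone would expect this trial to settle whether surgery is cost-effective. A reader of Study design, Objectives and the Strengths and limitations box would expect early estimates that help to plan a later evaluation. Both cannot be the purpose.

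The difference affects what the final report may say. The Data analysis section labels the clinical comparisons as descriptive and exploratory. The Health economic analysis section carries no limit of that kind of its own. As it stands, a statement that surgery is, or is not, cost-effective would be within plan even if the interval around it were very wide. The Dissemination policy says that policy makers will be told the results, so such a statement could be given more weight than the data can bear.

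**Working it through.** **1. Reproduce the plan's own figures (Sample size calculation).**

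- Recruited: 100 screened × 0.80 eligible × 0.60 recruited = 48. Completers: 48 × 0.90 = 43.2, stated as 43.
- Recruitment rate: SE = √(0.6 × 0.4 / 80) = 5.5%; exact 95% CI for 48/80 is 48.4% to 70.8%.
- Retention: 43/48 = 89.6%; SE = √(0.896 × 0.104 / 48) = 4.4%; exact 95% CI 77.3% to 96.5%.
- TUG: SE = 8/√43 = 1.22 s; chi-square 95% CI for the SD on 42 df, 6.60 to 10.17.
- RMDQ: SE = 6/√43 = 0.91; 95% CI for the SD, 4.95 to 7.63.

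All agree with the article. They are precisions for one pooled group. None concerns a difference between arms, and none concerns cost, QALY or ICER.

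**2. Precision of a between-arm contrast.** Cost-effectiveness is a comparison of arms. With 1:1 allocation, 43 completers split as 21 v 22. For any outcome with a common SD:

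- SE of the difference = SD × √(1/21 + 1/22) = 0.305 SD.
- 95% CI half-width = t(0.975, 41 df) × 0.305 SD = 2.02 × 0.305 SD = 0.62 SD.
- Difference detectable with 80% power, two-sided 5% = (1.960 + 0.842) × 0.305 SD = 0.85 SD.
- Power at a true difference of 0.5 SD is 37%; 80% power there needs 63 per arm.

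**3. On the article's own SDs.**

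| Outcome | SD | SE of pooled mean | SE of difference | 95% half-width | Detectable, 80% power |
|---|---|---|---|---|---|
| TUG | 8 s | 1.22 s | 2.44 s | 4.9 s | 6.8 s |
| RMDQ | 6 | 0.91 | 1.83 | 3.7 | 5.1 |

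The SE of the contrast is twice the SE quoted in the Sample size calculation.

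**4. Illustration in money.** The article gives no SD for costs or QALYs, so these inputs are assumptions: QALY SD 0.05 to 0.10, cost SD £3,000 to £8,000, no correlation between them, and a value (λ) of £20,000 to £30,000 per QALY. The SD of net benefit is √[(λ × SD of QALY)² + (SD of cost)²].

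- Low end: √[(20,000 × 0.05)² + 3,000²] = £3,162; half-width 0.616 × 3,162 ≈ £1,950 per patient.
- High end: √[(30,000 × 0.10)² + 8,000²] = £8,544; half-width 0.616 × 8,544 ≈ £5,260 per patient.

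This only restates 0.62 SD in pounds. The argument rests on step 2, which needs none of these assumptions.

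**5. Direction of any departure from 43.** The Study procedures section restricts participants who lack capacity to clinically assessed questionnaires. If EQ-5D is treated as self-reported, the number with usable QALYs would fall below 43 and the intervals would widen.

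**The case against.** The strongest defence is that the planned analysis is not a hypothesis test. The Health economic analysis section specifies an ICER with a 95% interval, one-way, two-way and probabilistic sensitivity analyses, and acceptability curves. These estimate and display uncertainty, and they can properly be reported from an unpowered study. A between-group economic analysis was also always intended: Study design plans an evaluation, and the Abstract and the Economic evaluation section both mention economic comparison of the groups. The Abstract calls the analysis largely descriptive. All of this stands. It protects the methods, but it does not reconcile the verb *determine* with an evaluation labelled preliminary.

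Several stronger readings are tempting, and the documents do not support them.

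- A reader might infer that the trial claims it will prove clinical effectiveness. That rests on the Discussion sentence alone. It follows a remark about the future trial, and its closing words can mean value for money in addition to effectiveness. The explicit statements on power point the other way. The Health economic analysis sentence, which says within-trial, is the firm evidence.
- A reader might infer that the economic component was meant only as a test of data collection. Study design says otherwise.
- A reader might infer that 43 completers could never yield a conclusion. No cost or QALY variability is given, and an effect of about 0.85 SD or more could well be detected.
- A reader might fear that an unfavourable ICER would stop the definitive trial. The Dissemination policy ties the funding application to feasibility, and nothing in the article makes cost-effectiveness a progression criterion.

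**Conclusion.** The point holds as a conflict of stated purpose. The Health economic analysis section promises a determination of cost-effectiveness that Study design, Objectives, the Strengths and limitations box, Data analysis and the end of the Discussion do not support. A 95% half-width of about 0.62 SD for any between-arm mean difference makes a firm conclusion unlikely to be supportable. That figure assumes 43 completers split 21 v 22, a common SD and an unadjusted comparison of means. The sterling range depends on assumed SDs and is illustrative only.

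The sample size figures are correct for what they describe, and the planned economic outputs are sound as description. The primary feasibility outcomes are unaffected. The correction still matters, because it changes what the trial may conclude.

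**What to change.** In Health economic analysis, replace the promise to determine cost-effectiveness with wording such as: *will provide preliminary estimates of incremental costs and QALYs, with their uncertainty, to inform the definitive trial; no conclusion on cost-effectiveness will be drawn*. Reword the Discussion sentence on value for money to match, without suggesting that this trial will demonstrate either value for money or clinical effectiveness.

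Keep the ICER, the sensitivity analyses and the acceptability curves, and label them as descriptive. There is no need to make data completeness the main economic output instead: Feasibility study outcomes and Data analysis already provide for reporting it, and displacing the ICER would be a change of outcome rather than of wording.

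The change needs no new data, participants or analyses. Its cost is that the stated aim of the economic component becomes less ambitious.
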